### Randomization and blinding

After baseline data collection, eligible classrooms from different schools will be randomly assigned to the intervention or the control group, by a random sequence generated using IBM-SPSS Statistical software. The personnel responsible for randomizing will be blinded to participants. Schools (directors, teachers and children) and families also will be blinded to their intervention or control group.

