**Methods:**

Eligible classrooms within schools from Vitoria-Gasteiz (Basque Country, Spain) will be randomly assigned to the intervention (classrooms *n* = 4; children *n* = 86) or control (classrooms *n* = 4; children *n* = 86) group. The intervention group will receive 14 sessions of 60 min during an academic year (October to June). These sessions, designed by a multidisciplinary team, are based on TPB and are directed at modifying determinants of behavior (attitudes, subjective norms, perceived behavioral control and intention of consumption), and intake of FV itself. Both the process and the evolution of consumption and determinants of behavior will be evaluated (before, during, shortly after and a year after) using validated surveys, 7 day food records, 24 h reminders and questionnaires.

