## Methods

### Design

A cluster randomized controlled trial will be carried out over an academic year at school level. Classrooms from different schools and schools themselves will be the clusters of the study. Clustering was chosen because this is the easiest way to implement an intervention program at school level. In this way the phenomenon of contamination between children from the same classrooms is avoided.

Whole classes (a minimum of 26 children per classroom) from different schools will be part of the intervention or control group. The control group allows us to analyze the direct effect of the intervention and to discard an increase of FV intake by seasonality (first measurements will be in October and final ones in June) or other factors. The study was approved by the Ethic Committee of the University of the Basque Country (CEISH/262/2014/[name]) and all parents or legal guardians and school directors and teachers will be sent an informed consent before the study starts. Written informed consents will be sent to parents or legal guardians through the children. After having received consents, the collection of the first data will be carried out followed by the randomized allocation of classrooms.

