### Sample size

In order to provide a power of 90% to detect an effect size (Cohen’s d) of at least 0.5 servings/day, 172 participants (86 in the intervention group and 86 in the control group) are required. Based in the dropout of similar studies [28–30], the final sample size is increased by 20% to reach 206 children (8 classrooms with a minimum of 26 children per class).

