### Statistical analysis

Descriptive statistics will be carried out to describe baseline characteristics of intervention and control group to assure comparability between groups.

Intra-group and inter-group FV intake differences at T0, T1, T2 and T3, will be analyzed by Student’s *t* test or non-parametric tests (Wilcoxon signed-rank test and Mann–Whitney U test). The same tests will be carried out to study the evolution of determinants of eating behavior (attitude, subjective norms, perceived behavioral control and intention) at different times.

To understand the relationship between determinants of behavior and behavior itself (FV consumption), multiple linear regression and structural equation modeling (SEM) analysis will be done at different times. Covariance of classic relationship of TPB determinants will be proposed. It will allow us to check the validity of the proposed model, as well as the influence of each determinant on the others and its significance. Changing models will be made by using difference on TPB determinants between different times.

Model validity will be established by comparative fit index (CFI), root mean square-error of approximation (RMSEA) and chi square/degrees of freedom (χ2/df). A good model will be determined by high values of CFI (> 0.90), low values of RMSEA (< 0.10) and χ2/df values from 1 to 3 [35, 36].

Multiple linear regression will be used to study the effect of social demographic variables in the effectiveness of the intervention.

Statistical analyses will be made using STATA 14.0, IBM-SPSS 24.0 and AMOS 24.0 statistical software. IC of 95% and significance level of *p* < 0.05 will be assumed.

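### No step in the stated design or analysis controls a chance baseline gap between the 4 v 4 classrooms, although baseline intake is collected before allocation; adjust the between-group comparison for it.

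*Protocol article*

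**What the plan says.** The order of events is given twice. Design: "After having received consents, the collection of the first data will be carried out followed by the randomized allocation of classrooms". Randomization and blinding: "After baseline data collection, eligible classrooms from different schools will be randomly assigned to the intervention or the control group", and this is done "by a random sequence generated using IBM-SPSS Statistical software". The Abstract fixes the arm sizes: classrooms are "randomly assigned to the intervention (classrooms *n* = 4; children *n* = 86" children), with the same numbers for control.

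Design also names schools as a level of clustering: "Classrooms from different schools and schools themselves will be the clusters of the study". No section describes balancing the arms on school, social background or baseline intake.

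Statistical analysis says baseline characteristics will be described "to assure comparability between groups". It then names Student's t test, or Wilcoxon and Mann–Whitney tests, for FV intake within and between groups at T0, T1, T2 and T3. Multiple linear regression is named for the behavioural determinants and for the effect of social variables on effectiveness. It is not named for the comparison between arms.

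**The concern.** With four classrooms per arm, random allocation can leave the arms visibly different in baseline intake or social mix. Participants states that schools are chosen to be representative in ethnicity and socio-economic status, so differences between classrooms are to be expected. A descriptive table can show an imbalance, but it cannot prevent or correct one.

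Two places could deal with it: the allocation, since baseline intake is scheduled to be in hand before the draw, and the analysis, by adjustment. The article describes neither. The stated between-group test at T2 would then carry whatever part of a baseline gap persists to June. In a single 4 v 4 draw this could hide or imitate a material part of the target effect.

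**Working it through.** **Inputs from the article.** 8 classrooms, 4 per arm (Abstract); at least 26 children per class, d = 0.5, 90% power, 172 children raised by 20% to 206 (Sample size); significance level 0.05 (Statistical analysis).

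**Assumptions.** Two-sided test. The article gives no ICC, so 0, 0.02, 0.05 and 0.10 are shown. The threshold of 0.25 SD, half of d = 0.5, is a choice made here.

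**The plan's own figure.** A two-sample t calculation with d = 0.5, two-sided 0.05 and 90% power gives 85.03 per arm, rounded up to 86, so 172 in all. 172 × 1.2 = 206.4, and 8 × 26 = 208. The stated numbers reproduce, which supports reading 0.5 as a standardised effect.

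**Chance gap with no balancing.** In SD units:
- variance of a class mean, V = ICC + (1 − ICC)/26
- SD of the arm difference = √(2V/4)
- P(|gap| > 0.25) = 2 × [1 − Φ(0.25/SD)]

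| ICC | V | SD of gap | 0.25/SD | P(gap > 0.25 SD) |
|---|---|---|---|---|
| 0 | 0.0385 | 0.139 | 1.80 | 7% |
| 0.02 | 0.0577 | 0.170 | 1.47 | 14% |
| 0.05 | 0.0865 | 0.208 | 1.20 | 23% |
| 0.10 | 0.1346 | 0.259 | 0.96 | 34% |

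A simulation over all C(8,4) = 70 splits (20,000 sets of class means) agrees. With 172/8 = 21.5 children per class the chances are 10%, 17%, 25% and 35%.

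Sample size labels the 0.5 both as Cohen's d and as servings/day. If it means raw servings, the chance of a gap above 0.25 servings at ICC 0.05 is 13%, 23%, 42% and 55% for an assumed SD of 0.8, 1.0, 1.5 and 2.0 servings.

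**What reaches follow-up.** If a fraction b of a baseline gap persists, the unadjusted comparison shifts by b × gap. No value of b is given. For illustration, a 0.25 SD gap with b = 0.3, 0.5 and 0.7 shifts the result by 0.075, 0.125 and 0.175 SD, which is 15%, 25% and 35% of d = 0.5.

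**Constrained draw.** Keeping the 42 best-balanced of the 70 splits and drawing one of them (simulated):

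| ICC | No balancing | Balance on intake only | Balance equally on intake and socio-economic level |
|---|---|---|---|
| 0.02 | 14% | 0.1% | about 2–3% |
| 0.05 | 23% | 1.0% | about 6–7% |
| 0.10 | 34% | 5% | about 14–16% |

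The ranges in the last column are for a correlation of 0.5 to 0 between the two balancing variables. At ICC 0.05 the SD of the gap falls from 0.21 to 0.11 (intake only) or 0.13–0.14 (both).

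**Size of the constrained set.** The smallest two-sided permutation p is 2/70 = 0.029 with all splits, 2/42 = 0.048 with 42, 2/40 = 0.050 with 40, and 2/16 = 0.125 with the 16 splits left by pair-matching.

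**The case against.** **Silence is not proof of simple randomisation.** A reader might infer that allocation is unrestricted. The article does not say so. The planned 4 v 4 split is itself a restriction, since independent coin tosses would give it only 70/256 = 27% of the time, and a condensed article may leave further detail to the full protocol. This stands: the point is only that no balancing is described. The calculation already assumes a 4:4 split, so no figure changes.

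**A chance gap is not bias.** Also right. Over repeated randomisation the comparison of arms is not shifted by imbalance. The cost is lost precision and a possible shift in the one result obtained, limited by how well baseline intake predicts later intake.

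**The gap would be seen.** The between-group test at T0 would show it. But seeing a gap does not remove it from the T1, T2 and T3 comparisons.

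**Allocation is probably over.** Registration was retrospective, dated 17/01/2018, and Trial status gives December 2018 as the end. T3 falls in June, a year after T2. If T3 lies within the study period, it was June 2018 at the latest, so T2 was June 2017 and T0 September 2016 at the latest. A change to allocation would then come too late. This stands, and it is why the analysis change leads.

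**Random allocation of classrooms without balancing is valid.** True; constraint is an efficiency gain. The absence of both balancing and adjustment is what leaves the gap uncontrolled.

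**Conclusion.** The point holds in limited form. Neither the described allocation nor the stated between-group tests deal with a chance baseline gap, although the data to do so are collected before the draw. With 26 children per class, the chance of a gap above 0.25 SD is about 14% to 34% for ICC 0.02 to 0.10, and 7% if classrooms do not differ at all.

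A reader might go further and call such a gap quite likely. On the standardised reading of the target it stays below one half at every ICC shown, at roughly one in four for ICC 0.05. It passes one half only under the raw-servings reading with a large SD. Nor do the documents support saying that the trial is biased, or that a baseline gap passes in full to follow-up: no baseline-to-follow-up correlation is given. The figures rest on the assumed ICC, on class size, and on roughly normal class means.

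**What to change.** **Main change, open whatever the state of allocation.** Replace the unadjusted between-group tests of FV intake at T1, T2 and T3 with a comparison adjusted for each child's T0 FV intake that also accounts for classroom clustering. Reword the sentence on descriptive statistics so that they describe comparability rather than assure it. No new data are needed. The cost is a revised analysis paragraph and a clustered analysis based on only 8 classrooms, which needs a small-sample method. If any restriction was used in the draw, state it and reflect it in the analysis.

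**Only if allocation is still open.** List the 70 possible 4:4 splits, score each on balance in classroom-mean baseline intake (and socio-economic level if wanted), keep at least the 42 best, and draw one at random. Avoid pair-matching: with 16 splits a permutation test cannot reach 0.05. Balancing on intake alone gives the larger cut in the intake gap; adding socio-economic level gives up some of it to balance the second variable.

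This option has real costs. About 208 seven-day food records must be coded before the draw, in the short interval between baseline and the first sessions. The analysis must respect the constraint. A classroom-level model with an intercept, arm and two balancing variables leaves only 8 − 4 = 4 degrees of freedom.

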### Study procedure

The intervention program will last one academic year. After randomization, meetings will be held with teachers of each classroom to describe the specific program to be carried out by each classroom without telling them which group they belong to (control or intervention) and to set the dates of sessions and evaluation procedures. Teachers of the intervention groups will receive some training, as they are models for children. All intervention and control sessions will be held by the same nutritionist, and data collection at baseline (T0: September), during (T1: January) and after (T2: June) intervention will be performed by the same researcher. To check any long-term effect, the measurements will be carried out one year after the end of the intervention (T3: June). Diagram of the study timeline is presented in Fig. 1

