### Intervention design

Following baseline data collection and randomization, the intervention group will start receiving program lessons every 15 days. Intervention group will receive 14 sessions of one hour over an academic year, from a nutritionist.

A multidisciplinary team designed the program. All materials, sessions and the program design are based on TPB and are respectful of gender, culture or religion. This theory states that people’s behavior is determined by their intentions, which in turn are influenced by attitudes, subjective norms and perceived behavioral control [24].Behavior: the action of eating FV.Intention: perceived likelihood of eating FV.Attitude: favorable or unfavorable judgments about eating FV. These judgments are determined by people’s beliefs, experiences and knowledge.Subjective norms: beliefs that most people who are important to children either approve or disapprove of them eating FV.Perceived behavioral control: perceptions of how much control they have over the behavior (action of eating FV).

In this study, these different variables are worked as described in Table 1.

**Table 1 Tab1:** Techniques to work behavioral determinants

Determinants of TPB	Behavior change technique	Example of how it is applied in the program
Attitude	Provide information on the behavior-health relationship	More FV ... “Why?” “Because they are healthy” They contribute ... “Fiber helps your gut work!”
	Work on positive / negative consequences of behavior (action / inaction)	The consequences of behavior are worked on according to the health benefits of various components of VF “To Do or Not To Do”
	Provide information about the relationship between pleasure and behavior	More information given about we eat what we like More FV ... “Which?” “The ones you like!”
	Work the ability to get pleasure through eating FV	The capacity of discriminating sensorial analysis is worked on, encouraging exploration “Explore with your senses” “Enjoy the ones you like!”
Subjective norms	Provide information about others behavior	Record the consumption of FV of all classmates on a sheet that all can see (“Fruitmeter”)
Perceived behavioral control	Work on instructions to increase autonomy or ability	Instructions are provided to make it easy reaching goals such as 5 a day: “If you eat fruit for breakfast... you’re already in way 1 out of 3!” “Food and dinners are times ... with vegetables on your plates!”

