	Work on situations that promote autonomy	Situations related to autonomy that promote the consumption of FV are practiced: participating in processes involved in producing, selling and preparing FV, e.g. cultivating, choosing and buying, cooking). “Get to know the orchard” “Participate! Choose and buy” “Have fun cooking”

Combining different theories in the program was discarded. This choice is based in a meta-analysis that analyzed the influence of behavioral theories on FV intervention effectiveness among children that found no association between the number of theories and consumption [27].

To make the program more effective, sessions were designed based on learning taxonomies [31], active learning methodologies and persuasion techniques (ELM: Elaboration Likelihood Model) [32]. All sessions have their own script for the nutritionist involved and all the scripts have the same structure (objectives, methodology, argument and resources). The script will be followed by the nutritionist with the aid of an audiovisual presentation, sheets for students, sheets for families, a goal-diary, FV’s folder, album and stickers, and material for specific sessions (e.g. FV as rewards at the end of each session and the “Fruitmeter”).

The proposed strategy has three axes of action: a) school activities, b) outside activities and c) home activities.School activities: Nine sessions will be held within the school (7 within the classroom and 2 FV cooking sessions in the dining room). Every month a “Fruitmeter” session will take place. In this activity, each classroom should write down their group FV mean intake using a tool called the “Fruitmeter”, which works by social pressure (subjective norms) to reach the objective of eating more FV. The “Fruitmeter” has poster format and will be hung in each classroom.Outside activities: Two visits to local product markets and two visits to local farmers. The last session will be held in a local theatre as the final FV program party.Home activities: a goal-diary which works with objectives related to FV consumption, e.g. to try a new vegetable this week or to eat fruit for breakfast three times per week, will be filled in at home with participants’ families. All worksheets that children use at school will be noted when they are reviewed at home with families.

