The control group only will receive two one-hour lessons during the academic year with general information about the benefits of FV intake. These sessions will be given by a nutritionist and will not be based on behavioral theories.

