### Outcomes

#### Primary outcome: Quantitative outcome

FV intake: FV (excluding potatoes and legumes) consumption will be measured by a validated self-fulfilling food record [33]. It provides information about standard servings of FV intake for 7 days, and it must be filled out by parents or legal guardians. To control self-completed food record data reliability, a researcher will make telephonic 24-h dietary recalls (goal-standard) on one randomly chosen day during the week in which the record is being filled.

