#### Secondary outcomes: Qualitative outcomes

Determinants of eating behavior: evolution of determinants proposed (attitude, subjective norms and perceived behavioral control) will be analyzed by a questionnaire designed according to bibliographic proposals [34]. Each determinant will be measured by a minimum of 3 items that will be answered by children marking a number on a 1–5 scale from “totally disagree” to “totally agree”. Validity of the survey will be checked by its internal consistency (Cronbach’s alpha).
Social demographic outcomes and families’ FV consumption habits: data will be collected by a questionnaire designed by the Department of Sociology 2 of the University of the Basque Country to obtain the following information:
Parental educational attainmentParental employment situationTheir perceived importance of their children’s FV intakeTheir level of knowledge concerning FV recommended intakeFV availability and accessibility at homeWhere children have their main mealChildren’s TV watching habits during mealsParents’ FV consumption habits.

Codified surveys will be sent by means of the children inside codified sealed envelopes. These will be filled out at home by parents and returned to school. Questionnaires of behavior determinants of behavior will be completed in 20 min by children at school under the supervision of a nutritionist. All the questionnaires will be completed at the three times described previously (T0, T1, T2) during the academic year and one year after intervention will be finished (T3).

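### Schools and families are described as blinded, but only the group label is withheld; parents who take part in the intervention at home also record the primary outcome

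*Protocol article*

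**What the plan says.** All references are to the protocol article.

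- **Randomization and blinding:** "Schools (directors, teachers and children) and families also will be blinded to their intervention or control group".
- **Study procedure:** after randomization, teachers have their own classroom's programme described to them "without telling them which group they belong to (control or intervention". The same section adds: "Teachers of the intervention groups will receive some training, as they are models for children".
- **Intervention design, intervention arm:** "Intervention group will receive 14 sessions of one hour over an academic year, from a nutritionist". The sessions include cooking, market visits, farm visits and a closing event in a theatre. A monthly activity uses the Fruitmeter, which "has poster format and will be hung in each classroom" and is meant to act through social pressure. At home, children and families fill in a diary of FV goals and go over the worksheets.
- **Intervention design, control arm:** "The control group only will receive two one-hour lessons during the academic year with general information about the benefits of FV intake".
- **Primary outcome:** FV intake comes from a 7-day food record, and "it must be filled out by parents or legal guardians". A researcher makes a telephone 24-h recall for one randomly chosen day of the record week, to control the reliability of the record.
- **Statistical analysis:** FV intake is compared within and between groups at T0, T1, T2 and T3 by t tests or non-parametric tests. The recall is not mentioned there.

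**The concern.** Blinding of participants matters most when they, or people close to them, report the endpoint. Here the quantity that the programme promotes, sets goals for and displays in the classroom is the same quantity that the household then reports. If a family taking part in the home activities records more generously than a family that is not, the difference enters the primary comparison as if it were an effect. Randomization does not remove it, because it arises after allocation. The Discussion would take an increase at the end of the programme as a sign that the programme is a valid and useful tool, so a reporting artefact could support its adoption. A reader who takes the blinding statement at face value would have little reason to look for one.

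**Working it through.** **1. Can the blinding statement hold?** The two arms, as the article describes them:

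| Feature | Intervention | Control |
|---|---|---|
| One-hour sessions | 14 (9 at school + 2 market + 2 farm + 1 theatre) | 2 |
| Teacher training | yes | none described |
| Fruitmeter poster | yes | none described |
| Home goal-diary and worksheets | yes | none described |
| Group label told to teachers | no | no |

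Contact time differs by a factor of 14/2 = 7. The last row is the only blinding measure in the text. Withholding a name hides the label, and perhaps the existence of a richer arm. It cannot hide from a teacher, child or parent what they themselves are doing every 15 days and at home. The statement under Randomization and blinding therefore cannot be squared with Study procedure and Intervention design.

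**2. Does this reach the primary outcome?** Parents or guardians fill in the record. Intervention families take part in the home component. Baseline is collected before allocation, so T0 records cannot be affected by allocation; records at T1, T2 and T3 can be.

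**3. Does the recall deal with it?** It covers one day of seven, and its stated purpose is the reliability of the record. The article does not say who answers it, whether the caller is masked to arm, or whether agreement is examined by arm. Agreement pooled over both arms could look acceptable while one arm over-records.

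**4. How much could it matter?** The article gives no SD and no bias figure, so this part is illustrative.

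The plan's own sample size comes first. With d = 0.5, 90% power and two-sided alpha 0.05 (sidedness assumed), the two-sample t test needs 85.03 per arm. That rounds up to 86 per arm, or 172 in total, as stated. The figure is reproduced and d is in SD units.

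With 86 per arm and individual-level analysis:

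- Standard error of the difference = √(2/86) = 0.1525 SD.
- Smallest significant observed difference = 1.96 × 0.1525 = 0.30 SD.
- With no true effect and over-recording b (in SD) in the intervention arm relative to control, P(significant, favouring intervention) = 1 − Φ(1.96 − b/0.1525).

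| Assumed b (SD) | b/0.1525 | P(significant, favourable) |
|---|---|---|
| 0 | 0 | 2.5% |
| 0.1 | 0.66 | about 10% |
| 0.2 | 1.31 | about 26% |
| 0.3 | 1.97 | about 50% |
| 0.5 | 3.28 | about 91% |

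Every value of b is an assumption, and clustering by classroom is ignored. The table shows only that a modest reporting difference would be enough to matter.

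**The case against.** The strongest defence has three parts.

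**The mechanism is stated.** Read together, Randomization and blinding and Study procedure describe withholding the label. Controls also have FV lessons from a nutritionist, so families in either arm may think they are simply in a programme, and nothing says that they can compare arms. This stands as a description of label-withholding, and it may soften the asymmetry. It does not rescue the word blinded: reporting can shift because a family is working on FV goals, whether or not it knows of another arm.

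**There is a safeguard, and the rest may be in the analysis plan.** It would be wrong to call the outcome unprotected, or to say that the recall serves only to check overall reliability; the text does not exclude analysis by arm. How agreement is tabulated is commonly left to a plan not shown here, so its absence is not itself the fault. The fault is a stated property that the design does not have, in a trial where that property bears on the primary outcome.

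**Several stronger readings go beyond the text.**

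- A reader might infer that the children's questionnaires, completed "under the supervision of a nutritionist", are supervised by the person who delivers the sessions. The article does not identify that nutritionist, and these are secondary outcomes.
- A reader might infer that parents are coached towards five portions a day. Those messages are listed as programme content; for families, only the diary and worksheets are described.
- A reader might set an assumed over-recording in servings against the 0.5 in Sample size. That figure is called a Cohen's d and reproduces as one. Without an SD it cannot be converted to servings.
- A reader might assume that a parent answers the recall, or that the T0 to T2 data collector makes it. Neither is stated.

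**Conclusion.** The blinding statement is wrong as written: schools, children and families have at most a group label withheld and are not blinded to the programme they receive. Because parents or guardians record the primary outcome and intervention families take part in the home activities, over-recording that differs by arm is possible, and a one-day recall described as a reliability check does not adequately address it.

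The document does not show that such bias will occur. Over-recording in the intervention arm is plausible, but neither its direction nor its size can be established. Open delivery is probably unavoidable for a programme of this kind and is not criticised here. The conclusion about blinding rests on the text alone; only the illustrative probabilities rest on assumed bias, two-sided testing and no clustering.

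**What to change.** 1. Under Randomization and blinding, describe schools, children and families as not blinded, with only the group label withheld.
2. State whether the person making the telephone recalls is masked to arm, and keep that person masked where existing staffing allows.
3. Pre-specify a between-arm comparison of record minus recall for the same day at T2, with T0 (collected before allocation) as a reference if the recall is made then too.
4. Pre-specify a sensitivity analysis of the T2 between-arm effect using the 24-h recall in place of the record.
5. State who answers the recall.

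The cost is wording, some care in assigning calls, and two analyses of data already planned. Intervention and sample size do not change. The drawback is that the recall covers one day, so it is noisier than a 7-day record, and it may rest on the same household's report. A family that inflates both by the same amount would show no difference. It is a partial check and should be reported as one.
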